### Outcomes

#### Primary outcomes

Mood instability (based on daily smartphone-based measures of mood)

#### Secondary outcomes

Patient-based questionnaires collected at baseline and after six months using the following questionnaires: quality of life according to WHO Quality of Life-BREF (WHOQoL) [42]; self-rated depressive according to the Major Depressive Inventory (MDI) [43]; self-rated manic symptoms according to the Altman Self-rating Scale for Mania [44]; perceived stress according to Cohen’s Perceived stress scale (PSS) [45]; satisfaction with care according to scores on the Verona Satisfaction Scale-Affective Disorder (VSS-A) [46]. The validity of each questionnaire is available from the references. Patients will be contacted by the study nurse in case on non-response of the questionnaires. Furthermore, we will collect information on adherence to the Danish national guidelines of medical treatment of bipolar disorder according to use of the three main maintenance mood stabilizers for bipolar disorder: lithium, lamotrigine or quetiapine [39]. Risk of psychiatric hospitalization and cumulated number and duration of psychiatric hospitalization according to data from the population-based Danish Psychiatric Central Research Register [40].

#### Tertiary outcomes (based on daily smartphone-based measures)

The following outcomes will be compared between the intervention group and the first control group.Mean stress (per month during the trial)Mean anxiety (per month during the trial)Mean irritability (per month during the trial)Mean activity (per month during the trial)Mean sleep duration (per month during the trial)Percentage of days with mixed moodPercentage of days with adherence to medication during the trial periodAdherence to smartphone-based self-monitoring during the trial period

No changes in outcome measures have been made after trial commencement. All patients will be contacted by the study nurse during the study to ensure retention and complete follow-up.

### Statistical power and sample size calculation

The statistical power and sample size were calculated using http://powerandsamplesize.com.

In the SmartBipolar trial with a follow-up period of 6 months, 1/3 will be randomized to daily smartphone-based monitoring and treatment, *including* a clinical feedback loop (intervention group). 1/3 will be randomized to daily smartphone-based monitoring, *without* a clinical feedback loop (control group), and 1/3 will be randomized to daily smartphone-based mood monitoring only (control group).

#### Mood instability

For each patient, a mood instability measure based on smartphone-based daily mood evaluations will be estimated for each day and aggregated in accordance with prior definitions by applying the root mean square successive difference (rMSSD) method [13, 14, 47]. The daily mood instability measures, reflecting the extent to which a daily and the previous day’s scores of self-monitored mood differed from one another during follow-up, were computed as the squared successive difference (SSD) of the reported values. Consequently, a daily mood instability measure could only be computed when consecutive daily values are present. The resulting SSD values will be aggregated for each patient as the root mean square successive difference (rMSSD), taking the square root of the mean of the SSD values [9, 11, 47, 48]. The instability measures will be computed following the original definition of the RMSSD score. Thus, differences between successive differences in mood are calculated, and then the values are squared, and the results are averaged before the square root of the total is obtained. The differences will be squared such that positive and negative differences do not cancel out when the values are aggregated by computing the mean. Squaring the values also puts more weight on larger differences. Finally, the square root of the mean puts the aggregated value back on the original scale. rMSSD is one of a few time-domain tools used to assess variability, the successive differences being neighboring mood scores. We decided to apply the RMSSD method following previous work. Thus, the mood instability measure do not reflect the severity of self-monitored data but rather the day-to-day changes by a statistical measure of a response to a question.

The primary outcome is mood instability between the intervention group and the two control groups—calculated as described above. Analyses will be done using intention-to-treat analyses. According to recent analyses, [15] mood instability in patients with bipolar disorder calculated using the definition above has a mean of 0.80 (SD 1.93). If mood instability decreases 0.2 units (SD 0.53) on the mood instability scale for trial arm I (the intervention group) versus trial arm II (the first control group) and trial arm I versus trial arm III (the second control group), respectively, a drop-out rate of 10% during the 6-month trial period (in accordance with the drop-out in our prior 6 months smartphone RCT) [30], a two-sided risk of type 1 error, *α* of 0.025 (since we will conduct two analyses between three groups with 0.05 level of significance in each analyses), a type 2 error risk, *β*, and a statistical power of 80%, the sample size (*N*) is calculated as *N* = 183. Thus, we need to allocate 67 patients in each of the tree arms of the trial and to randomize a total of 201 patients in the SmartBipolar trial.

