### Statistical methods

Data from all randomized patients is collected until dropout or the end of the trial period. The analysis will be carried out with an intention-to-treat (ITT) approach. Concerning the primary, secondary, and tertiary outcomes, analyses will be done employing linear mixed-effects regression models with a random intercept for each participant. Differences in outcomes between the intervention group and the control groups will be analyzed, firstly in an unadjusted model (except for potential differences in baseline values of the outcome variable in analyses) and then in models adjusted for the stratification variable CAG bipolar clinic and for age and sex as possible prognostic variables. If there is no statistically significant main effects of age and sex, these variables will be excluded from the final analyses. Multiple regression models will be conducted investigating differences in the proportion of psychiatric hospitalizations and the cumulated duration of all psychiatric hospitalizations during the sex-month trial period. Models will be conducted as unadjusted and adjusted for CAG bipolar clinic (stratification variable), age, and sex. Missing data will be handled as missing at random.

For all statistical analyses, the statistical threshold for significance is *p* ≤ 0.05 (two-tailed). Data will be managed by [name] and [name] and entered using RedCap®. All analyses will be done using SPSS, version 22.0 (IBM, New York, NY, USA), and STATA version 13 (StataCorp LP, College Station, TX, USA).

Data about potential and enrolled participants will be stored in RedCap® and on secure servers at Monsenso during and after the trial. Data collected during the course of the trial will be kept strictly confidential and only accessed by members of the trial team. Participants be allocated an individual trial identification number. Participant’s details will be stored in a secure database. Only researcher from the trial team will access the data set. Potentially, we will share anonymized trial data with other researchers to enable international prospective meta-analyses. This will be applied for separately.

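### The sample size section prints two unreconciled SDs for mood instability (1.93 and 0.53), and the stated 80% power is not reached with either

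*Protocol article*

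**What the plan says.** All of this stands in the Protocol article, under Statistical power and sample size calculation, subsection Mood instability.

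- **Endpoint.** Squared day-to-day mood differences are formed first, and then: "The resulting SSD values will be aggregated for each patient as the root mean square successive difference (rMSSD"). Each patient therefore contributes one score. The comparison is between arms: "The primary outcome is mood instability between the intervention group and the two control groups".
- **First SD.** With a citation: "mood instability in patients with bipolar disorder calculated using the definition above has a mean of 0.80 (SD 1.93").
- **Second SD.** In the next sentence: "If mood instability decreases 0.2 units (SD 0.53) on the mood instability scale for trial arm I" against each control arm. No source is given for 0.53, and it is not linked to 1.93.
- **Other inputs.** Alpha 0.025 two-sided for each of two comparisons, 80% power and 10% dropout.
- **Result.** N = 183, raised to 67 per arm and 201 in total.

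The mood scale (section on self-monitored measures in the intervention group) runs from −3 to +3. Table 1 schedules mood monitoring daily over the follow-up period. The Randomization and Statistical methods sections mention adjustment for baseline values of the outcome but give no correlation.

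**The concern.** A comparison of patient-level rMSSD between two arms needs the between-patient SD of that score, or a residual SD if a baseline covariate is used. The article prints two candidates that differ by a factor of 3.6 (1.93/0.53). It describes only the larger as the SD of mood instability as defined, and it uses the smaller. A reader cannot tell what 0.53 measures or whether it belongs to the endpoint.

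The power claim for the primary outcome is at stake. If power is well below 80%, a null result says much less about clinical feedback than the article implies. If the sourced mean and SD are on a different scale from rMSSD, the 0.2 target may be too, and its size relative to the endpoint is then unknown.

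**Working it through.** **Inputs (all from the article).** Difference d = 0.2; SD = 0.53 or 1.93; two-sided alpha 0.025 (z = 2.241); power 80% (z = 0.842); 67 randomised per arm; 183/3 = 61 evaluable per arm.

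**1. The plan's own figure.** The two-sample formula is n per arm = 2 × [(2.241 + 0.842) × SD/d]².

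- SD 0.53: 2 × (3.083 × 2.65)² = 133.5, so 134 per arm (402 in three arms; 149 per arm after dividing by 0.9).
- Without the factor 2: (3.083 × 2.65)² = 66.7, so 67. This equals the planned number per arm.
- Then 67 × 0.9 = 60.3, rounded up to 61, and 61 × 3 = 183.

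The article does not show this route, so it is an inference. Other settings with SD 0.53 do not give 61 per arm: two-sided alpha 0.05 gives 111, one-sided 0.05 gives 87, and pooling both controls gives 101 in the intervention arm.

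**2. Power at the planned size** (two-sample t-test, noncentral t, d = 0.2):

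| SD | alpha | 61 per arm | 67 per arm |
|---|---|---|---|
| 0.53 | 0.025 | 42.9% | 46.9% |
| 0.53 | 0.05 | 54.3% | 58.3% |
| 1.93 | 0.025 | 4.9% | 5.2% |
| 1.93 | 0.05 | 8.8% | 9.2% |

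The 0.05 rows are a sensitivity check, because the Statistical methods section sets a 0.05 threshold for all analyses. At 134 per arm and alpha 0.025, power is 79.8% with SD 0.53 and 8.2% with SD 1.93. Correcting the formula alone therefore does not settle the question of the SD.

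**3. Detectable difference** at 61 per arm, 80% power: 3.083 × SD × √(2/61) = 0.30 with SD 0.53 and 1.08 with SD 1.93.

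**4. SD that would give 80% at 61 per arm:** 0.2 / [3.083 × √(2/61)] = 0.36. The article contains no such figure.

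**5. Is 1.93 plausible for rMSSD?** On a −3 to +3 mood scale, rMSSD lies between 0 and 6. With mean 0.80 the largest possible variance is 0.80 × (6 − 0.80) = 4.16, so the largest SD is 2.04. It is reached only if 0.80/6 = 13% of patients score 6 and the rest score 0. Since 1.93² = 3.72, the printed SD uses 3.72/4.16 = 90% of that maximum. Daily squared differences range from 0 to 36, and an SD of 1.93 would not be extreme there.

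**6. Could 0.53 be derived from 1.93?** As a change-score SD it needs a correlation of 1 − 0.53²/(2 × 1.93²) = 0.96. As a covariance-adjusted residual SD it needs √(1 − 0.53²/1.93²) = 0.96. The article states no correlation.

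**7. If neither SD is right.** Assumed SDs, 61 per arm, alpha 0.025: 0.4 gives 69%, 0.6 gives 34%, 0.8 gives 19% and 1.0 gives 13%.

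**The case against.** The strongest reply is that 1.93 is probably not the SD of the endpoint at all. It sits near the ceiling for a 0 to 6 score with mean 0.80, the article defines a daily measure as well as the patient aggregate, and the cited source is not at hand. On that view 0.53 may simply be the patient-level SD, and the wording around it can be read as a between-arm difference with the outcome's SD. An article may also leave the source of an input to the full protocol.

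Much of this stands, and it rules out three stronger readings that a reader might infer:

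- **That the trial's power is about 5%.** The documents do not establish this. The figure holds only if 1.93 is the between-patient SD of rMSSD, which step 5 makes doubtful.
- **That the 80% claim fails only because 0.53 is unsupported.** It fails with 0.53 accepted in full.
- **That 0.53 must be a within-patient change SD, which the trial cannot form.** The text does not say what 0.53 is. Table 1 describes no mood recording before allocation, but early and late follow-up windows could be compared, although the early one would fall after allocation and the article defines none.

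The reply does not remove the contradiction. The article itself labels 1.93 as mood instability under its own definition, prints a different SD one sentence later, and attaches 80% power to a size that neither SD supports.

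**Conclusion.** The point holds in this form: the two SDs are unreconciled, the documents do not settle which one applies to patient-level rMSSD, and the stated 80% power is not reached with either. Power is about 43% to 47% with SD 0.53, where 134 evaluable per arm would be needed against about 61. It is about 5% with SD 1.93, as a conditional worst case. If 1.93 belongs to daily squared differences, the mean of 0.80, and possibly the 0.2 target, may also be on another scale.

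This assumes a two-sample comparison of one score per patient, difference 0.2, two-sided alpha 0.025, equal arms and no gain from covariates beyond what the printed SD already contains. Relaxing alpha to 0.05 raises power with SD 0.53 only to 54% to 58%. The account of how 67 per arm arose is inferred.

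**What to change.** In the sample size section:

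1. State which figure is the between-patient SD of patient-level rMSSD over follow-up, with its source. Correct or relabel the other.
2. Say whether the mean of 0.80 is patient-level rMSSD or a daily squared difference, and confirm that the 0.2 target is on the rMSSD scale.
3. Restate power and detectable difference with a two-sample formula at 67 randomised (about 61 evaluable) per arm. If no source settles the SD, use the pooled SD, ignoring arm, from patients already included (150 according to Trial status). This needs no arm comparison.
4. Keep N as planned, and report the primary result as an estimate with a confidence interval, read against the restated detectable difference.

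The cost is one pooled SD from data already collected and a rewritten paragraph, with no extra patients or visits. The downside is a less favourable stated power.

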### Randomization

#### Sequence generation

The company randomize.net is used for the randomization (http://randomize.net). The randomization is conducted by the staff at each center using an online procedure with stratification according to the psychiatric center. Each center can log on to a webpage by using a secure code and will conduct the randomization on-site. Patients included in the trial are randomized with a balanced allocation ratio of 1:1:1 to (1) daily smartphone-based monitoring and treatment *including* a clinical feedback loop (intervention group) or (2) daily smartphone-based monitoring *without* a clinical feedback loop (control group) or (3) daily smartphone-based mood monitoring only (control group) (Table 1). Block sizes are (unavailable to those who enroll participants or assign interventions) used to help preserve unpredictability [49, 50]. The study uses a stratified design, where patients are stratified according to the CAG bipolar clinic.

The statistical analyses will be adjusted for the stratification variable and age and sex as possible prognostic variables. Furthermore, in analyses on continuous variables, potential differences in baseline scores on the outcome in question will be included as a potential confounder. If there is no statistically significant main effects of age and sex, these variables will be excluded from the final statistical analyses.

### Blinding

Owing to the type of intervention in the SmartBipolar RCT, the patient, the patient’s healthcare provider, and the researchers are aware of the allocated randomization group. However, data on psychiatric hospitalization can be assessed, blinded to the intervention status, by the researchers. The researchers are responsible for data entry, data analyses, interpretation of analyses, and writing of papers are kept blinded to allocation during the handling of data.

### Statistical methods

Data from all randomized patients is collected until dropout or the end of the trial period. The analysis will be carried out with an intention-to-treat (ITT) approach. Concerning the primary, secondary, and tertiary outcomes, analyses will be done employing linear mixed-effects regression models with a random intercept for each participant. Differences in outcomes between the intervention group and the control groups will be analyzed, firstly in an unadjusted model (except for potential differences in baseline values of the outcome variable in analyses) and then in models adjusted for the stratification variable CAG bipolar clinic and for age and sex as possible prognostic variables. If there is no statistically significant main effects of age and sex, these variables will be excluded from the final analyses. Multiple regression models will be conducted investigating differences in the proportion of psychiatric hospitalizations and the cumulated duration of all psychiatric hospitalizations during the sex-month trial period. Models will be conducted as unadjusted and adjusted for CAG bipolar clinic (stratification variable), age, and sex. Missing data will be handled as missing at random.

For all statistical analyses, the statistical threshold for significance is *p* ≤ 0.05 (two-tailed). Data will be managed by [name] and [name] and entered using RedCap®. All analyses will be done using SPSS, version 22.0 (IBM, New York, NY, USA), and STATA version 13 (StataCorp LP, College Station, TX, USA).

Data about potential and enrolled participants will be stored in RedCap® and on secure servers at Monsenso during and after the trial. Data collected during the course of the trial will be kept strictly confidential and only accessed by members of the trial team. Participants be allocated an individual trial identification number. Participant’s details will be stored in a secure database. Only researcher from the trial team will access the data set. Potentially, we will share anonymized trial data with other researchers to enable international prospective meta-analyses. This will be applied for separately.

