**Assessments**		
Smartphone-based mood monitoring	Daily during the entire follow-up period	
Questionnaires^a^	X	X
Registry data^b^		X

^a^Quality of life according to WHO Quality of Life-BREF (WHOQOL-BREF); Self-rated depressive symptoms according to Major Depressive Inventory (MDI); Self-rated manic symptoms according to Altman Self Rating scale for Mania (ASRM); Perceived stress according to Cohen’s Perceived stress scale; Satisfaction with care according to Verona Satisfaction Scale-Affective Disorder (VSS-A)

^b^Number and duration of psychiatric hospitalization during follow-up, and use of medication during follow-up

The trial protocol describes a randomized controlled parallel-group superiority trial, the SmartBipolar trial, investigating the effect of smartphone-based monitoring and treatment in adult patients with bipolar disorder. The SmartBipolar trial is part of a larger CAG bipolar trial [20] and therefore has some of the same secondary and tertiary outcome measures.

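### Age and sex are kept or dropped by their p-values in the trial data, and the roles of clinic and baseline are worded loosely; the deciding model should have fixed covariates

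*Protocol article*

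**What the plan says.** The protocol article treats covariates in two places.

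- **Statistical methods.** The opening comparison of the arms is made "firstly in an unadjusted model (except for potential differences in baseline values of the outcome variable in analyses". A second step, which brings in clinic, uses "models adjusted for the stratification variable CAG bipolar clinic and for age and sex as possible prognostic variables". The selection rule is stated next: "If there is no statistically significant main effects of age and sex, these variables will be excluded from the final analyses".
- **Randomization, Sequence generation.** Analyses will be adjusted for the stratification variable, age and sex. The rule is repeated: "If there is no statistically significant main effects of age and sex, these variables will be excluded from the final statistical analyses". For continuous outcomes, "potential differences in baseline scores on the outcome in question will be included as a potential confounder".

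For the hospitalisation outcomes, Statistical methods says "Models will be conducted as unadjusted and adjusted for CAG bipolar clinic (stratification variable), age, and sex". The drop rule is not restated there.

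Table 1 schedules the questionnaires at 0 and 6 months. It schedules mood monitoring "Daily during the entire follow-up period". No mood series before randomisation is described.

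**The concern.** Three features of the text need attention.

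1. **The drop rule.** Whether age and sex stay is settled by tests on the trial's own outcome data. The final covariate set is unknown until those data are analysed, and it can differ from one outcome to the next. The text does not say whether age and sex are tested jointly or one at a time. Standard errors from the reduced model ignore the selection step.
2. **Clinic.** Randomisation is stratified by clinic and one section promises adjustment for it, yet the first model in the other section leaves it out.
3. **Baseline.** Describing baseline differences as potential, and baseline as a potential confounder, leaves open whether a baseline score always enters or enters only when the arms look different. In a randomised trial the reason to adjust is that the score is prognostic, whether or not the arms differ by chance.

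At stake are which estimate carries the conclusion, its error rate, and some power for outcomes that have a baseline score.

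**Working it through.** The plan gives no figure for this rule, so there is none to reproduce. The inputs from the article's sample size section are a difference of 0.2, an SD of 0.53, two-sided alpha 0.025 per comparison, and N = 183, that is 183/3 = 61 per arm. Statistical methods sets 0.05 for all analyses, so both levels are shown where available. The article gives no covariate effects or baseline correlation; these are assumed and varied.

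**Step 1. How often the rule would keep a covariate.** For correlation r with the outcome and n patients, P(keep) ≈ 1 − Φ(1.96 − atanh(r)·√(n − 3)). The text does not say whether all three arms share one model (n = 183) or each contrast is fitted separately (n = 122).

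| r | n = 122 | n = 183 |
|---|---|---|
| 0.10 | 0.19 | 0.27 |
| 0.15 | 0.38 | 0.53 |
| 0.20 | 0.60 | 0.78 |

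For modest effects, retention is uncertain in advance. This shows that the model varies with the data. It does not measure harm to the treatment estimate.

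**Step 2. What the rule does to the treatment estimate.** Least-squares simulation with 61 against 61 patients, one end-of-trial value each, and 10,000 runs per row. Age and sex each have correlation b with the outcome, there is no baseline term, and SDs are scaled to 0.53. The selected model drops age or sex when p > 0.05. Either means that the unadjusted or the selected model is significant.

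| b | P(at least one dropped) | SD, fixed model | SD, selected model | Type I at 0.025: fixed / selected / either | Either at 0.05 |
|---|---|---|---|---|---|
| 0 | 0.998 | 0.0972 | 0.0966 | 0.024 / 0.025 / 0.025 | 0.050 |
| 0.10 | 0.964 | 0.0964 | 0.0970 | 0.026 / 0.028 / 0.029 | 0.056 |
| 0.15 | 0.851 | 0.0952 | 0.0963 | 0.025 / 0.027 / 0.030 | 0.059 |
| 0.20 | 0.621 | 0.0942 | 0.0953 | 0.027 / 0.029 / 0.035 | 0.065 |
| 0.30 | 0.113 | 0.0880 | 0.0885 | 0.026 / 0.026 / 0.039 | 0.074 |

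The Monte Carlo standard error at 0.025 is √(0.025 × 0.975/10,000) ≈ 0.0016. The largest relative SD cost of selection is 0.0953/0.0942 ≈ 1.01. With no covariate effect the selected model is marginally more precise. At b = 0.30 the unadjusted model has SD 0.0971, and 0.0971/0.0880 ≈ 1.10, so relying on that model would cost about 10% in SD.

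**Step 3. Leaving clinic out of the first model.** If clinic explains a share R² of outcome variance, the unadjusted test after stratified randomisation has true size about 2·(1 − Φ(1.96/√(1 − R²))). At nominal 0.05 this is 0.044 for an assumed R² of 0.05 and 0.039 for 0.10. The error is conservative and applies only to that first model.

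**Step 4. Baseline.** With baseline-outcome correlation ρ, SE = 0.53·√(1 − ρ²)·√(2/61), and power at alpha 0.025 is Φ(0.2/SE − 2.241).

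| Assumed ρ | SE | Power, 61 per arm |
|---|---|---|
| baseline omitted | 0.0960 | 44% |
| 0.3 | 0.0915 | 48% |
| 0.5 | 0.0831 | 57% |
| 0.7 | 0.0685 | 75% |

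At ρ = 0.5, omission inflates the SE by 1/√0.75 ≈ 1.15. In simulation at ρ = 0.5 and a standardised difference of 0.2/0.53 = 0.377, always including baseline gave 55-57% power. Including it only when the arms differed gave 43-44%. The effect size is the one planned for mood instability. The article gives none for the questionnaires, so these powers are illustrative.

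**The case against.** The strongest defence is that the plan is less open than it looks. Both sections speak of final analyses, and the Randomization section promises adjustment for clinic, age and sex, so the adjusted model is the natural deciding one. The reduction looks at age and sex, never at the treatment effect. Naming a primary model is commonly left to the SAP, which is not shown. Much of this stands, and it limits what may be inferred:

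- **That precision is lost by the drop rule.** Not supported: the cost in step 2 is about 1% or less.
- **That the final model ignores the stratification factor.** Not supported: clinic is in the adjusted model and is not subject to the drop rule.
- **That several p-values are open to free choice.** The text states no either-model success rule. The 0.039 and 0.074 show what such a rule would do, not what is planned.
- **That baseline enters only when imbalanced.** The text says it will be included, and it is excepted even from the unadjusted model. Always included is at least as natural a reading.
- **That the covariate set can differ between the two contrasts.** This needs separate pairwise fits, which the text does not specify.

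The defence does not remove the drop rule. It is an explicit instruction given twice, and an SAP could cure it only by contradicting the article.

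**Conclusion.** The point holds as a correction of modest size. The rule makes the covariate set depend on the outcome data, the two sections differ on whether clinic is in every model, and the baseline sentence has two readings. Dropping age and sex by itself does little damage.

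Material harm is conditional. It arises if the unadjusted model is allowed to decide, or if a prognostic baseline enters only on imbalance. The second condition matters mainly for the questionnaire outcomes. With no pre-randomisation mood series described, a baseline gain for mood instability may not be available at all.

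The power of about 44% at 61 per arm is only the reference level for step 4. It is a sample-size matter that this rule does not cause; at alpha 0.05 the corresponding figure is about 55%. All sizes rest on assumed covariate effects and correlations and on one value per patient, not the full mixed model.

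**What to change.** Delete the exclusion sentence in both Sequence generation and Statistical methods. State one deciding model per outcome: arm, clinic, age and sex, plus the pre-randomisation score of that outcome wherever one is collected. Retain all terms whatever their significance or the observed imbalance. Replace the wording about potential baseline differences with a plain statement that the score is always included. Label the unadjusted model supportive, and say the same for the hospitalisation models.

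The cost is wording and a few degrees of freedom. At this version the trial was still recruiting (150 of 201 included) and no interim analysis was planned, so the change could precede any outcome comparison.

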### Hypotheses

In patients with bipolar disorder receiving specialized outpatient treatment for patients with bipolar disorders, using daily smartphone-based monitoring and treatment, *including* clinical feedback, improves mood instability and other clinically relevant outcomes (specified below) more than daily smartphone-based monitoring *without* clinical feedback or daily smartphone-based mood monitoring *only*.

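### The plan gives two thresholds for the two primary contrasts: 0.025 in the sample size and p ≤ 0.05 in the statistical methods

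*Protocol article*

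**What the plan says.** Three places in the protocol article bear on the threshold for the primary claim.

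- **Statistical power and sample size calculation, Mood instability.** The primary comparison is defined with two controls: "The primary outcome is mood instability between the intervention group and the two control groups". The calculation names arm I versus arm II "and trial arm I versus trial arm III (the second control group), respectively". It uses "a two-sided risk of type 1 error" with alpha "of 0.025 (since we will conduct two analyses between three groups with 0.05 level of significance in each analyses". The number of analyses is the reason given for 0.025, yet the same bracket puts the level at 0.05 for each analysis.
- **Statistical methods.** One sentence sets the decision rule: "For all statistical analyses, the statistical threshold for significance is" p ≤ 0.05, two-tailed. The section covers the primary, secondary and tertiary outcomes together. It makes no exception for the primary contrasts and names no procedure for testing two of them.
- **Hypotheses.** The intervention "improves mood instability and other clinically relevant outcomes (specified below) more than daily smartphone-based monitoring" without clinical feedback, *or* mood monitoring only. The Objectives section also joins the two comparators with *or* for mood instability, but with *and* for the questionnaire and register outcomes. Neither section says whether one contrast suffices for success or both are needed.

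**The concern.** The threshold for the primary outcome is the main decision rule of a confirmatory trial, and here it has two values. A contrast with p = 0.03 would be a positive result by the methods section and a negative one by the alpha on which the trial was sized. If this is left open, the choice could be made after the data are seen, in a trial whose primary outcome is self-reported by unblinded patients and whose findings are to be put directly into practice in the clinics. If the looser rule is used and either contrast can carry the claim, the false-positive rate of the primary claim exceeds 5%.

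**Working it through.** **Inputs from the article**
- Two primary contrasts, I vs II and I vs III, sharing arm I (Mood instability).
- Allocation 1:1:1 (Trial design and study organization).
- Two-sided alpha 0.025 in the sample size (Mood instability); 0.05 for all analyses (Statistical methods).
- Difference 0.2, SD 0.53, power 80%, N = 183, which is 183/3 = 61 per arm; 67 per arm randomized (Mood instability).

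**Step 1. Does the stated N show which alpha was used?**
The usual formula for two means is n per arm = 2 × [SD × (z(1−α/2) + z(0.80)) / difference]².
- α = 0.025: 2 × [0.53 × (2.241 + 0.842)/0.2]² = 133.5, so 134 per arm.
- α = 0.05: 2 × [0.53 × (1.960 + 0.842)/0.2]² = 110.2, so 111 per arm.

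Neither gives 61, so the N does not reproduce and cannot show which alpha was meant. That failure is a separate matter and does not affect this point.

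**Step 2. The two rules side by side**

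| Primary p-value | Alpha in the sample size (0.025) | Statistical methods (0.05) |
|---|---|---|
| ≤ 0.025 | significant | significant |
| above 0.025, up to 0.05 | not significant | significant |
| above 0.05 | not significant | not significant |

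The rules disagree in the middle row.

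**Step 3. Family-wise error if either contrast can carry the claim**
With equal arms and a common variance σ², each contrast has variance 2σ²/n and the covariance through arm I is σ²/n. The correlation is therefore (σ²/n)/(2σ²/n) = 0.5. When both nulls are true, family-wise error = 1 − P(|Z1| < c and |Z2| < c), with Z1 and Z2 bivariate normal.

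| Level per contrast | c | Correlation 0.5 | If independent | Upper bound |
|---|---|---|---|---|
| 0.05 | 1.960 | 9.1% | 1 − 0.95² = 9.75% | 10% |
| 0.025 | 2.241 | 4.6% | 1 − 0.975² = 4.9% | 5% |

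**Step 4. If both contrasts had to be significant**
With both tested at 0.05 and both nulls true, the chance that both are significant is 0.05 + 0.05 − 0.0907 = 0.009, or about 0.9%. There is no inflation under that rule.

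**Step 5. Power cost of the stricter threshold**
Take the plan's 61 evaluable per arm and d = 0.2/0.53 = 0.377. The expected test statistic is 0.2/(0.53 × √(2/61)) = 2.084.
- One contrast: Φ(2.084 − 1.960) = 55% at 0.05; Φ(2.084 − 2.241) = 44% at 0.025.
- At least one of two, both effects real: 71% at 0.05; 60% at 0.025.
- Both of two, both effects real: 27% with 0.025 for each; 37% with Holm.

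**The case against.** The strongest reply is that the plan does adjust. The sample size section adopts a Bonferroni-type 0.025 and explains it by the two analyses. On that view the bracket is a garbled form of 0.05 overall, and the sentence in Statistical methods is a generic one into which the adjustment was not carried. This is plausible, and it rules out saying that the document as a whole has no multiplicity control. It does not remove the conflict, because the methods sentence admits no exception and the bracket repeats its 0.05.

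A reader might infer that the trial's family-wise error simply is 9%. The documents do not support that. The figure requires the methods section to override the sample size section, a win on either contrast to count as success, and both nulls to be true. The *or* in Hypotheses and Objectives favours the either-contrast reading, and so does the alpha split, which would be needless if both wins were required. But better than A or B can also mean better than both in ordinary English, and no sentence decides it.

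It can also be argued that two distinct comparators with separate claims need no adjustment. That is a debated choice. The plan made the opposite one when it cited two analyses as the reason for 0.025, so it must follow that choice or withdraw it.

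Finally, an analysis plan that is not shown might settle the matter. It could add detail, but this is a rule stated in two incompatible ways, not one left unstated.

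**Conclusion.** The contradiction holds and needs to be fixed: the primary threshold is 0.025 in one place and 0.05 in two others, and results with p between the two are classified differently. This part rests on the text alone.

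The inflation is conditional. It is about 9.1% against 4.6%, assuming that Statistical methods governs, that either contrast suffices, that both nulls are true, and that the contrasts correlate at 0.5 from equal arms with a common variance. If both contrasts were required, there would be no inflation.

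The point concerns the two primary contrasts only. It does not show that the 0.05 threshold for secondary and tertiary outcomes is wrong.

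**What to change.** 1. In Statistical methods, add a sentence for the primary outcome: each of the two primary contrasts (I vs II, I vs III) is tested at two-sided 0.025, and superiority is claimed separately for each contrast.
2. In the Mood instability section, correct the bracket to read 0.05 overall and 0.025 in each analysis.
3. Leave p ≤ 0.05 for secondary and tertiary outcomes as it stands.

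As an option, replace the fixed 0.025 in item 1 by Holm: the smaller p-value is tested at 0.025 and, if it is significant, the other at 0.05. Holm also keeps the family-wise error within 5% and is more powerful for the second contrast, but it is not needed to remove the contradiction.

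The change should be made and dated before any outcome data are compared by arm.

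**Cost.** Two short edits, with no change to the stated N, which was already set at 0.025. The real price is power relative to p ≤ 0.05. At 61 per arm and d = 0.377, single-contrast power is about 44% instead of 55%, and the chance of at least one win is about 60% instead of 71%. Holm does not recover the loss on the first win.
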